### Outcome measures

Information on demographic data, smoking habits, occupational status, professional exposure to asthma risk factors/triggers, concomitant diseases and therapies and asthma history will be collected during the first visit. Due to the observational nature of the study, the spirometry is not included in the study procedures but it will be performed according to the doctor’s evaluation. If available, the lung function parameters will be collected in the case report form. The following self-administered tools will be used for the assessment of asthma control, quality of life and adherence to therapy.

#### Six-item asthma control questionnaire (ACQ)

The six-item ACQ [13] includes a measure of the top five asthma symptoms (woken at night by symptoms, day-time symptoms, limitation of daily activities, shortness of breath and wheeze) and the use of quick-relief bronchodilators. The asthma control level will be evaluated according to the following thresholds: controlled asthma: ACQ score ≤ 0.75; partly controlled asthma: 0.75 < ACQ score <1.5; uncontrolled asthma: ACQ score ≥ 1.5.

As long as many factors are to be considered when a symptom-based approach is being used to achieve optimal disease control [22]*,* the possible reasons for poor control (e.g. comorbidities, seasonal worsening, depression, etc.) will be collected both according to the doctors’ and patients’ opinions using a multiple choice system from a drop down list.

#### Mini asthma quality of life questionnaire (mini-AQLQ)

The mini-AQLQ [23] has been developed to measure the impact of asthma and its treatment that are most troublesome to adults with asthma according to the patient’s perspective and contains 15 questions in four domains: symptoms, activity limitation, emotional function and environmental stimuli. The overall score ranges from 7 (indicating no impairment due to asthma) to 1 (indicating a severe impairment due to asthma).

#### Four-item morisky medication adherence scale (MMAS-4)

The MMAS-4 is a validated scale that estimates the risk of medication non-adherence and consists of four items assessing reasons for non-adherence: forgetfulness, carelessness, feeling better and feeling worse. The Morisky score ranges between 0 (highly adherent) and 4 (highly non-adherent) [24,25].

### Pharmacological therapies

Due to the observational design of the study, antiasthmatic treatments prescribed to patients during the study will be at the discretion of the study physicians according to their clinical judgment and local standards. Antiasthmatic therapies will be recorded in terms of active ingredient, dosage, duration and method of administration. Adverse drug reactions (ADRs) will be recorded for the entire study duration according to the local laws of each country.

### Use of healthcare resources and exacerbations

The number of outpatient visits, hospitalisations and emergency department visits due to asthma will be recorded in order to relate the use of healthcare resources to the level of asthma control.

Information on the number of severe exacerbations, defined as the deterioration in asthma resulting in a hospitalisation or an emergency room visit or the need for systemic steroids for more than 3 days because of asthma, will also be collected [26].

### Data management

Clinical data will be recorded via Electronic Data Capture (EDC) using the HyperSuite-Hypernet XMR® system, an electronic CRF (eCRF). Paper questionnaires (six-item ACQ, mini AQLQ and MMAS-4) filled in by patients during the clinic visits will be entered into the clinical database by independent data-entry operators.

### Sample size

Based on available data from the literature, the proportion of patients with controlled asthma at initial visit (defined as an ACQ score ≤ 0.75) is expected to be about 37.5% [15]. Considering that patients with uncontrolled and partly controlled asthma at the cross-sectional phase visit will be included in the prospective phase, the percentage of patients with controlled asthma at month 12 is expected to be approximately 45% [27].

By enrolling 8,150 patients, it is expected that 5,094 patients should have uncontrolled/partly controlled asthma at the cross-sectional phase visit. The proportion of patients expected to drop out, for any reason, during the 12-month longitudinal phase is 20%. Therefore, 4,075 patients should be evaluable at month 12, which allows estimating the expected 45% of patients reaching asthma control at the end of longitudinal phase with a precision of ± 1.5% (two-sided 95% CI).

With regard to the assessment of quality of life, a standard deviation (SD) for the Mini AQLQ overall score of approximately 1.21 units can be estimated from the literature [28]. If 4,075 patients are evaluable for the analysis of the Mini AQLQ overall score from the cross-sectional phase visit, then the distance from the boundaries of the two-sided 95% CI to the point estimate will be 0.037 units. Therefore, considering the expected patients reaching asthma control at the end of the longitudinal phase, the distance from the boundaries of the two-sided 95% CI to the point estimate will be 0.055 units.

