### Study population

The study population will include approximately 8,150 patients attending about 160 outpatient hospitals or General Practice clinics distributed across 12 European countries (Austria, Belgium, France, Germany, Greece, Hungary, Italy, the Netherlands, Poland, Spain, Turkey and the United Kingdom). At least 400 patients in about eight centres will be enrolled in each participating country. Consecutive patients visiting the centre during the estimated 12-month recruitment period will be enrolled.

Male and female adult (aged ≥18 years) patients with a clinical diagnosis of asthma (according to GINA guidelines and confirmed by a chest physician) for at least 6 months, and receiving the same antiasthmatic drugs in the last 4 weeks before enrolment, will be eligible for study participation after signing the informed consent.

Patients participating in a clinical trial within the previous 4 weeks or patients suffering from conditions and illnesses that might interfere with the study purpose, according to the investigator’s evaluation, will be excluded from the study.

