### Statistical analysis

All recorded variables will be tabulated using summary statistics for continuous variables and frequency tables (absolute and relative) for categorical variables. All outcomes will be stratified by country.

Logistic regression analysis will be used to analyse binary variables (e.g. the association between the asthma control level and quality of life in the cross-sectional phase). Models will include confounding factors if identified by the exploratory analysis. As measures of association between the response variable (e.g. the asthma control level) and the independent variables, the odds ratios (ORs) with the relative 95% CI along with the p-value will be reported. For continuous variables, the estimated OR will be expressed for a change of *c* units in the covariate.

The analyses of the results of the longitudinal phase will be conducted using mixed-effect models (SAS Proc MIXED) to estimate the means of the changes in the scores over time from the cross-sectional phase visit.

The healthcare costs will be evaluated by descriptive analysis, considering the time frames of 3 months before the cross-sectional phase visit and the longitudinal phase period.

The number of severe exacerbations in the last 12 months before the cross-sectional phase visit and the number of severe exacerbations per patient/year at each visit will be descriptively analysed overall and by level of asthma control. The rate of severe exacerbations per patient/year will be calculated as the total number of experienced severe exacerbations over the longitudinal phase on total number of days of observation of patients at risk. The time to first asthma severe exacerbation during the longitudinal phase will be analysed with the Kaplan-Meier survival analysis, and their significance by the log-rank test. Predictors of exacerbations will be analysed by means of a multivariate logistic model. A stepwise selection approach will be used to identify the most significant prognostic factors and to eliminate the unimportant ones. Using this methodology, a final predictive model containing just the important variables will be created.

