We chose the 6-item ACQ for the evaluation of asthma control because it is applicable to all adults with asthma, is considered reliable and reproducible. It has been fully validated for use in both clinical practice and clinical trials, and the minimum clinically important difference has been established [13]. The ACQ also has strong discriminative properties, i.e. it is able to detect small differences between patients with different levels of asthma control and it is very sensitive to within-patient changes in asthma control over time [27]. The overall population included in the LIAISON study will be representative of the European real-life setting. A sample size of at least 400 patients enrolled in at least eight centres in each country will also allow reliable country-specific analyses of data collected in a number of sites that are representative of the entire National territory in all involved countries [6]. Previous reports have included a limited number of sites [12] or a smaller number of patients in some countries than in others [6], while other studies have been performed in sites with non-homogeneous distribution in the same country [21].

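### The planned precision figures treat patients as independent although they are recruited within about 160 centres, so they are too narrow for any positive centre correlation, modestly for the pooled estimate and more so by country

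*Protocol article*

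**What the plan says.** All of this is in the protocol article.

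- **Study population:** the sample is "approximately 8,150 patients attending about 160 outpatient hospitals or General Practice clinics distributed across 12 European countries". Within a centre, "Consecutive patients visiting the centre during the estimated 12-month recruitment period will be enrolled". By country, "At least 400 patients in about eight centres will be enrolled in each participating country".
- **Pharmacological therapies:** treatment is left to the study physician's judgment and to local standards.
- **Sample size:** the proportion controlled at the first visit "is expected to be about 37.5" per cent. With 20% dropout, 4,075 patients are evaluable at month 12, which is said to allow "estimating the expected 45% of patients reaching asthma control at the end of longitudinal phase with a precision of ± 1.5" percentage points (two-sided 95% CI). For the Mini-AQLQ, with an SD of 1.21, the half-widths given are 0.037 and 0.055 units. The section mentions no centre, ICC or design effect.
- **Statistical analysis:** outcomes are stratified by country, and "Logistic regression analysis will be used to analyse binary variables". Mixed-effect models are named for changes in scores over time.
- **Discussion:** "A sample size of at least 400 patients enrolled in at least eight centres in each country will also allow reliable country-specific analyses". No country-level half-width is given.

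**The concern.** Patients at the same clinic share physicians, setting (hospital or general practice), referral pattern and prescribing habits. Their control status and quality of life are therefore likely to be correlated. A precision formula for independent patients ignores this and gives an interval that is too short.

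The stakes differ by level. The pooled month-12 proportion rests on many centres, so the loss is limited. A country estimate may rest on about eight centres, and country estimates support the article's aim of comparing care between countries. At that level the interval can become wide enough to change what can be said.

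**Working it through.** **Inputs from the article:** 8,150 patients; about 160 centres; 12 countries; a minimum of 400 patients in about eight centres per country; 37.5% controlled at entry; 20% dropout; 45% controlled at month 12; Mini-AQLQ SD 1.21.

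**Assumed:** centre ICC of 0.01 to 0.10, because the documents give none, and equal centre sizes. Unequal sizes would generally widen the results further.

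**Step 1. Reproduce the stated figures, assuming independence.**
- Not controlled at entry: 8,150 × 0.625 = 5,094. Evaluable at month 12: 8,150 × 0.625 × 0.8 = 4,075.
- Proportion: 1.96 × √(0.45 × 0.55 / 4,075) = 1.53 points, stated as 1.5.
- Mini-AQLQ: 1.96 × 1.21 / √4,075 = 0.037. With 0.45 × 4,075 = 1,834 patients, 1.96 × 1.21 / √1,834 = 0.055.

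All three match, so all three use a design effect of exactly 1.

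**Step 2. Allow for centres.** Design effect DE = 1 + (m − 1) × ICC, where m is the number of patients per centre. The half-width is multiplied by √DE. At month 12, m = 4,075 / 160 = 25.5. An interval computed as if patients were independent covers 2Φ(1.96/√DE) − 1.

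| Assumed ICC | DE | Pooled month-12 half-width | Actual coverage of a nominal 95% interval that ignores centre |
|---|---|---|---|
| 0.01 | 1.24 | ±1.70 | 92% |
| 0.02 | 1.49 | ±1.86 | 89% |
| 0.05 | 2.22 | ±2.28 | 81% |
| 0.10 | 3.45 | ±2.84 | 71% |

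An ICC of about 0.03 takes the half-width to 2.0 points.

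If the same ICC range is assumed for the Mini-AQLQ, 0.037 becomes 0.041 to 0.069 (m = 25.5). The 0.055 becomes 0.058 to 0.079 (m = 1,834 / 160 = 11.5).

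**Step 3. Country minimum.** Cross-sectional: 400 patients, m = 400 / 8 = 50, p = 0.375. Month 12: 400 × 0.625 × 0.8 = 200 patients, m = 200 / 8 = 25, p = 0.45. Half-widths in points:

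| Assumed ICC | Cross-sectional, normal quantile | Cross-sectional, t on 7 df | Month 12, normal quantile | Month 12, t on 7 df |
|---|---|---|---|---|
| 0 (independent) | ±4.7 | – | ±6.9 | – |
| 0.01 | ±5.8 | ±7.0 | ±7.7 | ±9.3 |
| 0.02 | ±6.7 | ±8.1 | ±8.4 | ±10.1 |
| 0.05 | ±8.8 | ±10.6 | ±10.2 | ±12.3 |
| 0.10 | ±11.5 | ±13.9 | ±12.7 | ±15.3 |

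The t quantile applies when the variance is estimated from eight centres.

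**Step 4. Average country.** 8,150 / 12 = 679 patients in 160 / 12 = 13.3 centres, with 4,075 / 12 = 340 evaluable at month 12. At ICC 0.05:
- Cross-sectional: 1.96 × √(0.375 × 0.625 / 679 × 3.50) = ±6.8 points.
- Month 12: 1.96 × √(0.45 × 0.55 / 340 × 2.22) = ±7.9 points.

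**The case against.** Several objections are sound and limit the point.

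- **The arithmetic is right.** The weakness is an unstated assumption, not a miscalculation. This stands.
- **The size rests on an assumed ICC.** At 0.01 the pooled loss is only from ±1.5 to ±1.7 points. The differences between countries that the Discussion reports (65% to 40% not well controlled) do not measure centre correlation within a country, because stratifying by country removes that component. This stands. The direction does not depend on the value, as any positive ICC widens the interval.
- **Eight centres is a minimum.** The average country does better (Step 4), and the 200 evaluable patients assume that every country has the pooled 62.5% not controlled. The Discussion states no interval, so the country claim is unsupported rather than numerically wrong. This stands.
- **Nothing hinges on ±1.5.** The study is descriptive, and the Sample size section sets no test or margin that a wider interval would fail. This stands for the pooled estimate.

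Two stronger readings are tempting, and the documents do not support them. A reader might infer that the analysis will ignore centre because the Statistical analysis section does not mention it. A condensed article commonly leaves that to the full protocol or SAP, so silence does not show omission. A reader might also infer that every odds ratio will have too short an interval. The design effect above applies to means and proportions. For a covariate that varies within centres the inflation is roughly 1 + (m − 1) × ICC(outcome) × ICC(covariate), which is close to 1 when the covariate itself clusters little. Most factors the article names, such as smoking and adherence, are patient-level.

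An unseen SAP that adjusts for centre would not rescue the planned precision, which is already fixed in the Sample size section.

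**Conclusion.** The point holds as a moderate issue. The three planned precision figures describe a sample of independent patients, which is not the sample the design collects. With about 25 evaluable patients per centre, and ICC assumed between 0.01 and 0.10, the pooled month-12 half-width is about ±1.7 to ±2.8 points, so the main estimate remains useful.

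The practical weight is at country level. At the guaranteed minimum the half-width is about ±5.8 to ±11.5 points cross-sectionally and ±7.7 to ±12.7 at month 12, and wider with 7 degrees of freedom. For an average country at ICC 0.05 it is about ±6.8 and ±7.9. Calling such analyses reliable without giving a half-width is not supported. The exact sizes depend on the assumed ICC and on equal centre sizes.

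**What to change.** 1. In Sample size, restate the half-widths for the proportion and the Mini-AQLQ under a stated ICC range. For the month-12 proportion this is about ±1.7 to ±2.8 points for 0.01 to 0.10.
2. Compute confidence intervals for proportions and means with centre as the cluster within country strata.
3. In the regression models, use a random centre effect or cluster-robust standard errors. This matters most for covariates that vary mainly between centres. If the full protocol or SAP already does this, a sentence saying so is enough.
4. In the Discussion, replace the claim of reliability with the half-width that 400 patients in eight centres deliver, using a t quantile suited to the number of centres.

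The cost is a less favourable stated precision and slightly more analysis work. No extra patients are needed.

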## Objectives

Table 1 summarises the primary and secondary objectives of the study. The primary objectives of the cross-sectional phase are to evaluate the proportions of patients with controlled, partly controlled and uncontrolled asthma, and to assess the health-related quality of life and the factors associated with asthma control in a real-life population of asthmatic patients.

**Table 1 T1:** Primary and secondary objectives to be investigated

	**Cross-sectional phase**	**Longitudinal phase**
**Primary objectives**	• Prevalence of patients with controlled or uncontrolled/partly controlled asthma	• Proportions of patients with controlled, partly controlled and uncontrolled asthma after 12 months from the cross-sectional phase visit
	• Health-related quality of life	• Proportion of patients with uncontrolled/partly controlled asthma switching to controlled asthma after 12 months from the cross-sectional phase visit
	• Factors associated with asthma control	• Changes in quality of life after 12 months
		• Factors associated with the gain of asthma control
**Secondary objectives**	• Proportion of asthmatic smokers and their level of asthma control	• Association between (current) level of asthma control and (future) risk of exacerbations
	• Antiasthmatic therapies	• Relation between change in asthma control and change in rate of exacerbations during the longitudinal phase (including stratified analyses according to GINA treatment level)
	• Medication adherence	• Antiasthmatic therapies
	• Healthcare costs over 3 months before the cross-sectional phase visit	• Proportion of patients with uncontrolled/partly controlled asthma that reach control after 3 and 6 months from cross-sectional phase visit
	• Rate of severe exacerbations in the last 12 months before the cross-sectional phase visit	• Medication adherence
	• Reasons for poor control according to the Investigators’ and the patients’ opinion	• Healthcare costs
	• Lung function parameters, if available	• Rate of severe exacerbations and the time to first severe exacerbation
		• Reasons for poor control according to the Investigators’ and the patients’ opinion
		• Lung function parameters, if available

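### The Mini-AQLQ precision figures (0.037 and 0.055) are computed correctly, but their patient numbers or SD do not match the primary quality-of-life objectives

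*Protocol article*

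**What the plan says.** Table 1 of the protocol article (Objectives) lists health-related quality of life as a primary objective in both phases. In the cross-sectional phase it concerns the whole enrolled population. In the longitudinal phase it reads "Changes in quality of life after 12 months". The Statistical analysis section agrees with the latter: mixed-effect models are to estimate mean changes in the scores from the cross-sectional visit.

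The Sample size section takes its SD from a cited source: "a standard deviation (SD) for the Mini AQLQ overall score of approximately 1.21 units can be estimated from the literature". The first precision statement begins "If 4,075 patients are evaluable for the analysis of the Mini AQLQ overall score from the cross-sectional phase visit" and concludes that "the distance from the boundaries of the two-sided 95% CI to the point estimate will be 0.037 units". The second, "considering the expected patients reaching asthma control at the end of the longitudinal phase", gives 0.055 units.

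The same section explains where 4,075 comes from. It states "By enrolling 8,150 patients, it is expected that 5,094 patients should have uncontrolled/partly controlled asthma at the cross-sectional phase visit", then removes the expected dropout of 20% over the 12-month phase and describes the remainder as evaluable at month 12.

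**The concern.** A planning precision needs a sample size and an SD that belong to the quantity being estimated. Here the wording points to the cross-sectional visit, while the sample size belongs to month 12. By that point two groups have been removed: patients already controlled at entry, and dropouts during follow-up. Neither loss affects a mean score measured at the first visit.

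The phrase could instead be read as change from that visit, which is the longitudinal objective. The sample size then fits, but the SD must be that of a within-patient change, and the document calls 1.21 the SD of the overall score.

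The second figure covers only patients who reach control, a group defined by a month-12 outcome. Neither primary quality-of-life objective is restricted to them.

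These are the only precision figures the article gives for two primary objectives. As written, a reader cannot tell which estimand 0.037 describes, and no precision is clearly stated for the 12-month change that the study intends to report.

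**Working it through.** **Inputs, all from the Sample size section**
- Enrolled: 8,150.
- Controlled at the initial visit: 37.5%, so 62.5% enter the longitudinal phase.
- Dropout over 12 months: 20%.
- Expected to reach control at month 12: 45%.
- SD of the Mini-AQLQ overall score: 1.21.
- Two-sided 95% confidence interval, z = 1.96.

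**Step 1: patient numbers**
- 8,150 × 0.625 = 5,093.75, stated as 5,094.
- 8,150 × 0.625 × 0.8 = 4,075, as stated.
- 0.45 × 4,075 = 1,833.75, about 1,834 patients reaching control.

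**Step 2: reproduce the plan's figures.** Half-width = 1.96 × SD / √n.
- n = 4,075: 1.96 × 1.21 / √4,075 = 0.0372, stated as 0.037.
- n = 1,834: 1.96 × 1.21 / √1,834 = 0.0554, stated as 0.055.

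Both reproduce, which confirms that the plan used 4,075 and about 1,834 patients, each with SD 1.21.

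**Step 3: reading 0.037 as the mean score at the cross-sectional visit**
- All enrolled, n = 8,150: 1.96 × 1.21 / √8,150 = 0.0263.
- Only those not controlled at entry, n = 5,094: 1.96 × 1.21 / √5,094 = 0.0332.

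Because 8,150 is twice 4,075, the stated half-width is √2 ≈ 1.41 times the one that matches the cross-sectional objective. Step 3 assumes simple random sampling.

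**Step 4: reading 0.037 as the mean change at month 12.** Here n = 4,075. If the SD is 1.21 at both visits and r is the correlation between them, SD of change = 1.21 × √(2(1 − r)). The documents give no r, so these values are assumptions:

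| Assumed r | SD of change | Half-width, n = 4,075 |
|---|---|---|
| 0.3 | 1.432 | 0.044 |
| 0.5 | 1.210 | 0.037 |
| 0.6 | 1.082 | 0.033 |
| 0.7 | 0.937 | 0.029 |
| 0.8 | 0.765 | 0.023 |

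Under equal variances, the stated 0.037 is exact only at r = 0.5. It is too wide above that value and too narrow below it.

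**Step 5: the 0.055 figure.** It takes the SD of the general score and applies it to patients selected for having reached control by month 12. The text offers it as a consequence of the preceding sentence, but the only thing that has changed is the smaller n.

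**The case against.** The strongest defence is that 0.037 is coherent on a third reading. The text after Table 1 words the prospective objective more loosely, as assessing health-related quality of life without mention of change. A mean score at month 12 in 4,075 evaluable patients, with a score SD of 1.21, does have a half-width of 0.037. This stands as arithmetic, and it rules out saying that the figure fits nothing. It does not rescue the sentence, which refers to the cross-sectional visit, while Table 1 and the Statistical analysis section both specify change.

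The figure also errs mostly on the cautious side. For the cross-sectional mean under simple random sampling, the study would be more precise than stated. For the change, 0.037 is an upper bound whenever r is at least 0.5. That is fair, although nothing in the document shows that r is that high.

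The 0.055 figure is openly labelled as concerning patients expected to reach control, and the Discussion names the effect of control on quality of life as an interest of the study. It is therefore a legitimate supplementary figure, and a demand to delete it would go too far.

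The calculation in Step 4 has its own weakness. It applies 1.21 at both visits to a cohort that excludes controlled patients, so the range is illustrative only.

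A reader might also want to widen every figure for clustering by centre. The documents give no intraclass correlation, so any multiplier would be an outside assumption, and the same question would apply to the ±1.5% for the control proportion. It is a separate matter and is not part of this point.

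**Conclusion.** The point holds as a mismatch between inputs and objectives. A reader might infer a calculation error, but the documents do not support that, since both figures reproduce. Nor do they support the inference that the study is the wrong size. The 4,075 is justified first by the control proportion: 1.96 × √(0.45 × 0.55 / 4,075) = 1.53%, in line with the stated ±1.5%.

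What is wrong as written is that 0.037 is attached to the cross-sectional visit with the month-12 sample size. The figure matching the cross-sectional objective is ±0.026, given n = 8,150, SD 1.21 and simple random sampling. For the 12-month change, 0.037 is right only if the SD of change is also about 1.21. Under equal variances and assumed correlations of 0.3 to 0.8, the half-width runs from 0.044 to 0.023. Whether the cited source's 1.21 is in fact an SD of change cannot be checked here; the document calls it the SD of the score. The 0.055 describes a subgroup that neither primary quality-of-life objective addresses.

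The practical effect is small. Every half-width calculated for the two objectives is below 0.05 on a scale from 1 to 7. The correction is still worth making, because it concerns stated figures for primary objectives.

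**What to change.** In the Sample size section:
1. For the cross-sectional mean Mini-AQLQ score, state n = 8,150 and a half-width of ±0.026, and say that this assumes simple random sampling.
2. For the mean change at month 12, state n = 4,075 and 1.96 × SD of change / √4,075. Use an explicit, sourced SD of change, or show a range of correlations with the equal-variance assumption named.
3. Keep 0.055 if wanted, labelled as a supplementary figure for patients expected to reach control, and say that it borrows the SD of the general score.

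The cost is a few restated lines of text. Enrolment, visits and analyses are unaffected.
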